### Main objective

- To estimate the improvement of health-related quality of life in patients involved in the EFICAR programme and the control group, and also any difference between the two groups in terms of improvement in quality of life, which would be an effect that could be attributed to exercise.

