### Protocol for the intervention group

The EFICAR group differs from the control group only in terms of the exercise programme, which has two phases. The exercise programme is a combination of "high-intensity interval training" and "muscular strength training". It has been demonstrated that high intensity aerobic exercise leads to better aerobic and cardiovascular changes than light/moderate exercise in patients with HF [13,14].

• *1st PHASE *(12 weeks, 3 sessions/week): for the first three months, patients carry out a progressive exercise programme of 36 sessions under the supervision of the nurse, starting at low intensity (first month) and increasing it month by month (See Figure 2).

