### Outcome measures

These measurements are made by an interviewer blind to the group the patient has been assigned to.

*Primary outcome measure *(basal, 3, 6 and 12 months):

• Changes in health-related quality of life (HRQL) (SF36, Minnesota Living with Heart Failure Questionnaire - MLHFQ).

The HRQL questionnaire is measured blindly with self-administered questionnaires: the Spanish version of the SF-36 and MLHFQ. Both questionnaires will be filled out before and after the intervention. SF-36 generates an 8-dimension health profile and two summary scores for the physical and mental components. The 21 items from the MLHFQ record the perception of the patient in relation to how the HF affects the emotional, social, physical and mental dimensions of their HRQL. Both questionnaires have been validated in the Spanish population [20,21].

*Secondary outcome measures *(basal, 3, 6 and 12 months):

• Functional capacity, measured with the 6-minute Walking Test [22].

• Muscular strength, measured by dynamometry [23].

• Body composition (body fat and muscle percentage) [23].

• Structural changes in the heart (natriuretic peptide levels, prognostic factor) [24].

*Predictor or Confounding variables*: sex, age, comorbidity and risk factors.

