### Quality control

Various processes were undertaken in order to guarantee the quality of the data of the study, and thus maximise the validity and reliability of the programme and measurement of outcomes. These are:

• Preparation of documents for the study process: fieldwork manuals, nursing and intervention measurements, educational leaflets and list of measurements.

• Written documentation: electronic and hard copies of the protocol, signed consent forms, and patient results stored under lock and key. All written information, including letters sent to patients is standardised in each of the centres.

• Training for those in charge of the standardisation of the study process.

• Training for nurses concerning the study characteristics and procedures, and, in particular, the quality of life interview to be given to the patients.

• Holding of regular meetings: with the coordinator of the study (daily) and with the principal investigator of each collaborating centre (weekly).

• Quarterly meetings and daily contact by email with the members of the EFICAR group and all the participating centres.

• Monthly production of progress reports.

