### Limitations

Despite the study not dealing with mortality and hospital admissions as a main measure, it is important to highlight that the HF-Action study has demonstrated that the effect of exercise on mortality is minimal. Given this, the functional capacity and quality of life are the most important aspects to improve in the rehabilitation of these patients.

Also, the structure of the study renders impossible blinding the participants and the interveners, however, blind outcome assessors will be used.

The monitoring of this intervention and data collection is complex, and therefore data will be collected using many relevant quality control processes, and standardization of the intervention will be assured. In addition, to avoid contamination of the control group, interveners will be trained, and a pilot study will also be carried out.

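### The primary quality-of-life outcome is labelled blind although unblinded patients score it themselves; its mode of collection is described inconsistently, and the arms differ by a programme, not by exercise alone

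*Protocol article*

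**What the plan says.** All places are in the protocol article.

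- **Blinding of the primary outcome.** Outcome measures opens with "These measurements are made by an interviewer blind to the group the patient has been assigned to" and then says of the primary outcome "The HRQL questionnaire is measured blindly with self-administered questionnaires". Study design likewise lists quality of life among the measurements taken blind. Outcome measures also explains that the MLHFQ items capture the patient's own view of how heart failure affects them.
- **Blinding of patients.** Limitations says "the structure of the study renders impossible blinding the participants and the interveners, however, blind outcome assessors will be used".
- **Mode of collection.** Quality control lists nurse training, "in particular, the quality of life interview to be given to the patients".
- **Who delivers the programme.** Protocol for the intervention group says "patients carry out a progressive exercise programme of 36 sessions under the supervision of the nurse". The following text adds that each patient is regularly told how they are progressing.
- **Attribution.** The same section says "The EFICAR group differs from the control group only in terms of the exercise programme". Main objective describes the between-group difference as one "which would be an effect that could be attributed to exercise", and Secondary objectives uses similar language. Statistical analysis is more careful and speaks of the effect attributable to the intervention.

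**The concern.** When a questionnaire is self-completed, the patient is the outcome assessor. A patient who knows the allocation makes the assessment unblinded, whoever hands out or collects the form. The protocol nonetheless calls the measurement blind. Limitations goes on to present blind assessors as the answer to unblinded participants, without saying that this answer does not reach the primary outcome.

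Three things are at stake:

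- A reader would take the primary result as protected by blind assessment when it is not.
- Six centres could reasonably collect the questionnaires in different ways.
- A between-group difference could be reported as an effect of exercise when the compared arms also differ in supervised contact and feedback.

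**Working it through.** **1. Blinding: the passages side by side.**

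| Question | Answer in the protocol | Section |
|---|---|---|
| Is the primary outcome blind? | Yes | Study design; Outcome measures |
| Who scores it? | The patient (self-administered) | Outcome measures |
| Is the patient blind? | No, not possible | Limitations |
| What protects against bias? | Blind outcome assessors | Limitations |

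The second and third rows together contradict the first, and the fourth does not act on an outcome the patient scores.

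**2. Mode of collection.** Outcome measures gives both a blind interviewer and self-administration. Quality control gives an interview for which nurses are trained. Protocol for the intervention group has a nurse supervising the sessions. No section says whether the nurses trained for the interview are separate from those supervising sessions.

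**3. Contact in the two arms.** Study design gives both groups health education and self-care support. Protocol for the control group sets appointments at 4, 8, 12, 24 and 48 weeks. The Discussion section on optimising regular care sets nurse monitoring weekly in month 1, every other week in months 2 and 3, then monthly. That is roughly 4 + 4 = 8 monitoring contacts in the first three months. The EFICAR arm adds 12 weeks × 3 sessions = 36 supervised sessions in the same period, with feedback on progress.

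**4. How small a difference becomes significant.** Inputs from Sample size: 300 per group, 20% losses (300 × 0.8 = 240), target difference 3, SD 10, two-sided 5%, within-person correlation 0.6. Normal approximation throughout.

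- Standard error of the difference: SE = SD × √(2/n).
- The plan's own figure first. With 300 per group, SE = 10 × √(2/300) = 0.816 and power = Φ(3/0.816 − 1.96) = 95.7%. With 240 per group, SE = 0.913 and power = Φ(3/0.913 − 1.96) = 90.8%. The stated power above 80% holds.
- Smallest significant difference with 240 per group: 1.96 × 0.913 = 1.79 points.
- With adjustment for baseline: SD = 10 × √(1 − 0.6²) = 8, SE = 8 × √(2/240) = 0.730, smallest significant difference 1.43 points.

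**5. Illustration of a reporting bias.** Assume no true effect and a shift b in reported scores in the EFICAR arm. The documents give no value for b; the values below are assumptions. The chance of a significant result is Φ(b/SE − 1.96) + Φ(−b/SE − 1.96).

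| Assumed b (points) | 240 per arm, SD 10 | 240 per arm, baseline-adjusted SD 8 |
|---|---|---|
| 0 | 5.0% | 5.0% |
| 0.5 | 8.5% | 10.5% |
| 1 | 19.5% | 27.8% |
| 2 | 59.1% | 78.2% |

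Worked line for b = 1, SD 10: 1/0.913 = 1.095; Φ(−0.865) + Φ(−3.055) = 0.194 + 0.001 = 0.195.

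**The case against.** - **The unblinding is disclosed and unavoidable.** Limitations says plainly that participants cannot be blinded, no exercise trial could do otherwise, and the blind label can be read as describing the staff who collect the form. This stands in part: the design is not at fault for unblinded patients. What remains is that the label is attached to the questionnaire measurement itself, and Limitations does not link unblinded patients to the self-scored outcome.
- **The conflict in mode may be only apparent.** A blind interviewer could run the visit at which patients fill in the forms. That is possible, but the text does not say it, and training nurses to give an interview points the other way.
- **A reader might infer that the nurses who supervise exercise also interview the patients.** The documents do not show this. Outcome measures and Limitations distinguish blind assessors from interveners. Overlap is not excluded, and no more can be said.
- **Controls receive substantial structured attention.** This is correct, and it narrows the contrast. The supervised phase also lasts 12 weeks, while the outcome is measured again at 6 and 12 months. An imbalance in contact nevertheless remains.
- **A reader might infer that every bias favours EFICAR.** Expectation would usually be thought to act that way, but the documents do not establish it. They name forces towards no difference: usual-care patients becoming more active in the earlier large trial (Background), and contamination of the control group (Limitations).
- **The bias sizes have no source.** This is true. Any shift inflates rejection in any unblinded trial of this precision. The table shows sensitivity, not that a bias exists.

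**Conclusion.** The point holds in a limited form. The protocol gives its primary outcome a property, blindness, that the design does not have, and relies on a safeguard that does not reach that outcome. The mode of collection needs reconciling between Outcome measures and Quality control. A between-group difference estimates the effect of the EFICAR programme, meaning exercise together with supervised contact and feedback.

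It would go too far to say that a difference could not be attributed to exercise at all. The size of any reporting bias is unknown, and Main objective says only that the effect could be so attributed. The supported statement is that it cannot be attributed to exercise alone.

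On size, differences of about 1.4 to 1.8 points (0.14 to 0.18 SD) would be significant against a target of 3 points, so a modest bias could matter. The rates of 8.5%, 19.5% and 59% rest wholly on assumed biases of 0.5, 1 and 2 points with no true effect, 240 per arm and SD 10. The sample size and power statement are unaffected.

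**What to change.** 1. **Study design, Outcome measures, Limitations:** state that SF-36 and MLHFQ are unblinded patient self-report. Keep the word blind for outcomes measured by a blinded assessor or a laboratory. Add to Limitations that blind assessors do not protect the primary outcome.
2. **Outcome measures and Quality control:** describe one mode of collection for all centres and visits. One option is self-completion, with forms handled by staff who do not deliver sessions and are blind to group. A named blinded interviewer would also resolve the conflict over mode, though the answers would still come from unblinded patients.
3. **Main objective and Secondary objectives:** word the conclusion as the effect of the EFICAR programme, in line with the wording already in Statistical analysis. Interpret the quality-of-life result with unblinded self-report named as a limitation, and with natriuretic peptide, already a secondary outcome at the same visits, as the more objective companion. The 6-minute walk depends on the effort of unblinded patients and is a weaker check.

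The cost is wording and one site instruction, with no new measurements. The downside is a more modest claim.

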### Adverse events

Provisional analysis of the data is performed by an independent committee to monitor safety. This committee will define the indicators in relation to mortality, hospital admissions and cardiac decompensation events, having independent access to the necessary data. The committee will be composed of people who are independent of the body in charge of the management of the study and of the researchers and will be blind to the assignment of patients to the comparison groups, will review the data every quarter and will make recommendations to the team directing the project with respect to the continuation or the interruption of the study.

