### • Safety Committee

The data will be provisionally analysed by an independent committee to monitor safety. This committee will be composed of people who are independent of the body in charge of the management of the study and of the researchers and will be blind to the assignment of patients to the comparison groups. It will define the indicators related to mortality, hospital admissions and decompensations, and will have independent access to the necessary data. It will review the data of study every quarter and will make recommendations to the team in charge of the project with respect to the continuation or interruption of the study.

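### The safety committee is blinded to assignment, so it cannot attribute an excess of deaths, admissions or decompensations to the exercise arm when it advises on continuing the trial

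*Protocol article*

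**What the plan says.** Two sections of the protocol article describe the committee in nearly the same terms: Adverse events (Methods/Design) and Safety Committee (Discussion).

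- **Task.** "Provisional analysis of the data is performed by an independent committee to monitor safety".
- **Material.** "This committee will define the indicators in relation to mortality, hospital admissions and cardiac decompensation events". It works "having independent access to the necessary data".
- **Output.** It "will make recommendations to the team directing the project with respect to the continuation or the interruption of the study".
- **Blinding.** In Adverse events the committee "will be blind to the assignment of patients to the comparison groups, will review the data every quarter". In the Discussion it again "will be blind to the assignment of patients to the comparison groups".

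Neither section mentions tables by arm, coded groups, an unblinded statistician or a way to break the blind.

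Two other statements matter. Protocol for the intervention group says: "The EFICAR group differs from the control group only in terms of the exercise programme, which has two phases". Limitations says that "the structure of the study renders impossible blinding the participants and the interveners", and adds that outcome assessors will be blind.

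**The concern.** The committee's recommendation turns on whether the trial is safe to continue. Both arms consist of patients with NYHA class II-IV heart failure on the same optimised care, so deaths, admissions and decompensations will occur in both. Exercise is the only thing that separates the arms, so any harm from it appears as more events in one arm than in the other. The stated blinding removes that comparison, or at least its direction, from the body asked to judge safety.

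Two errors become possible. A harmful programme could continue because its excess is hidden in the total. A harmless one could be interrupted because the background rate shared by both arms is high. The abstract names patient safety as a key challenge, and the Discussion states as an expectation that exercise adds no risk. The committee should be able to check that expectation.

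**Working it through.** The point rests on who sees assignment, not on a figure in the plan. The arithmetic shows what knowledge of the arm adds.

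**1. The plan's own safety benchmark.** Risks of the intervention gives a worst case of one clinical event per 3700 patient-hours of exercise and a 39% chance of an event per centre. Inputs: 300 exercisers (Sample size), six centres (Settings), 36 supervised sessions (Protocol for the intervention group), and 1 hour per session (assumed, as the readable text gives no total session length).

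- Per centre: 300/6 = 50 exercisers; 50 × 36 × 1 = 1800 h; 1 − exp(−1800/3700) = 38.5%. This agrees with 39%.
- Whole trial: 300 × 36 × 1 = 10,800 h; 10,800/3700 = 2.9 events.

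This benchmark applies to exercisers. Comparing observed events with it requires knowing which patients exercise, and the blinding clause withholds that.

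**2. What a pooled total can tell.** Assume a 12-month risk of 20% in controls and 30% in EFICAR. The documents give no such risks.

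- Controls: 300 × 0.20 = 60 events. EFICAR: 300 × 0.30 = 90 events. Total: 150/600 = 25%.
- The same 150 arises from 75 v 75 (no effect) and from 90 v 60 (benefit).

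**3. What the split by arm can tell.** For a single look at full follow-up, two-sided 5%, n per arm and p̄ the mean of the two risks:

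power ≈ Φ{ [|p₂ − p₁| − 1.96·√(2p̄(1 − p̄)/n)] / √([p₁(1 − p₁) + p₂(1 − p₂)]/n) }

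- 20% v 30%, n = 300: (0.100 − 1.96 × 0.03536)/0.03512 = 0.874; power 80.9%.
- 20% v 30%, n = 150: (0.100 − 1.96 × 0.0500)/0.04967 = 0.040; power 51.6%.
- 10% v 20%, n = 300: (0.100 − 1.96 × 0.02915)/0.02887 = 1.485; power 93.1%.

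Range over assumed control risks, 300 per arm:

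| Control risk | Relative risk 1.25 | Relative risk 1.5 |
|---|---|---|
| 10% | 16% | 46% |
| 20% | 31% | 81% |
| 30% | 49% | 97% |

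**4. Small excesses.** Adding about 3 events to 300 patients at a 20% background gives 20% v 21%. The upper tail is Φ[(0.010 − 1.96 × 0.03296)/0.03296] = 4.9% and the lower tail 1.2%, so power is about 6%. Seeing the arms would hardly help here.

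**5. The masked A/B reading.** With labels but no key, 60 v 90 is visible as a difference. Whether it means harm (EFICAR 90) or benefit (EFICAR 60) is not, and the two call for opposite advice.

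**The case against.** The strongest reply is that the text never says the committee sees only pooled counts. It analyses the data, sets its own indicators and has independent access to what it needs. Being blind to assignment could mean masked group labels, and a condensed article may leave report format and code-breaking to a charter. This stands in part: pooled reporting is only one of two readings. But masked labels without the key hide the direction, and a charter that gave the committee the key would contradict a rule stated twice here.

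A blinded committee is also not powerless. It can react to individual events or to a high overall rate. If the background were known to be exactly 20%, a pooled 25% in 600 patients would exceed it with about 85% power. The documents give no such background rate, however, and a raised total would still not point to exercise.

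Three stronger inferences are tempting, and the documents do not support them.

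- *The committee is the only safeguard.* The protocol also has exercise-test screening, a stabilisation phase before randomisation, supervised sessions with effort and symptom monitoring, scheduled nurse and medical follow-up, and emergency arrangements. An event during a supervised session would be recognised without unblinding anyone. None of these compares event rates between arms.
- *Blinding the committee has no use.* It can guard the judgement of individual events against prior belief, and this protocol states a strong belief that exercise is safe. That patients and interveners know the arm does not cancel this.
- *Deaths and admissions will never be compared by arm, because they are not among the listed outcomes.* Such an analysis may be left to the statistical analysis plan, which is not shown. Limitations says openly that these events are not a main measure.

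**Conclusion.** The point holds in limited form. As written in both sections, the committee must advise on continuation without being able to attribute an excess of events to the exercise programme. On the pooled reading it cannot see a difference between arms. On the masked-group reading it cannot tell the direction. This follows from a stated rule and from exercise being the only difference between arms. That the committee's safety task includes this comparison is an inference, but a sound one.

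The size can only be illustrated: about 81% power by arm for 20% v 30% at 300 per arm, and about 52% at 150 per arm, against a pooled 25% that fits harm, no effect or benefit equally. These figures assume the event risks and a single look with complete 12-month data. They do not describe the quarterly reviews. For small excesses, reports by arm would add little power. The primary estimate, sample size and primary analysis are unaffected. The issue is patient safety oversight, and it should be settled before the committee's first review.

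**What to change.** Replace the blinding clause in Adverse events and in Safety Committee with the same text in both places:

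- The independent committee receives closed quarterly reports of deaths, hospital admissions and decompensations by arm, either coded A/B with the key available to it or fully unblinded.
- The reports are prepared by someone who takes no part in the outcome analysis.
- The trial team sees only pooled safety data, and outcome assessors stay blind.

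The cost is a wording change and one table per quarter. The Randomisation section has the Primary Care Research Unit of Bizkaia assign patients, so it already holds the allocation list. Settings names the same unit as the centre for design and analysis, so the separation of the report's preparer has to be arranged explicitly. The price is that the committee loses masked judgement of individual events and that interim results by arm must be kept confidential. No stopping rule or other clinical rule is proposed.

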### Follow up period

One year since the beginning of the intervention.

### Sample size

A total of 600 patients will be recruited, 300 per group. This simple size gives a statistical power of higher than 80%, to enable any difference between the control and the intervention group greater than 3 with respect to the primary outcome scale from the physical functioning SF-36 and MLHQ to be found to be significant, with a significance level of 5% using the two-tailed Student's t test (standard deviations obtained from prior studies with similar population to that of our project: SD = 10 points of the quality of life questionnaires SF-36 and MLHQ) [12,25,26]. Given other reports, it can be expected that the losses during follow-up will be around 20%, the correlation between the measurements of the same individual 0.6 and the correlation intracentre 0.01.

